**Fig. 1 Fig1:**
[figure not shown]
Flowchart indicating the three patient groups with COPD and the process of study-inclusion and 5-year follow-up: (1) undiagnosed COPD at inclusion who underwent further assessment, (2) previously diagnosed with COPD at inclusion, (3) COPD at inclusion who declined further assessment

The app AIR MD algorithm selects the best of three forced expiratory manoeuvres. The app algorithm also informs the nurse about the precision grade and if the result is acceptable.

Participants with identified impaired lung function, that is a FEV1/FVC ratio below 0.7 or the values of FEV1 and/or FVC below 80% of the predicted value, will be referred to the respiratory outpatient clinic at the hospital for further diagnostic work-up. This referral protocol is applicable irrespective of whether the participant has a pre-existing lung condition or not. In cases where it is not feasible for patients to be seen at the respiratory outpatient clinic, they are instructed to contact their general practitioner for subsequent evaluation and management.

Finally, the social nurse asks the patient about their motivation to quit smoking. In addition, they receive information about available options for smoking cessation support, including hospital resources or referrals to cost-free municipal smoking cessation services.

Coordination regarding follow-up assessment, follow-up care, and general support from social nurses constitutes standard care and is not a part of the intervention but should be taken into account in interpreting the findings.

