#### Five-year follow-up outcome measures

At follow-up, we will report on whether:Opportunistic screening for COPD by social nurses has an impact on the rate of hospital contacts. This is assessed by examining the number of hospital contacts per person year within each year of the 5-year follow-up (both outpatient visits and hospitalizations) with a diagnosis related to COPD for three patient groups: (1) the group with no previous COPD diagnosis, impaired lung function at screening, and who underwent further assessment, (2) the group of patients with previous diagnosed COPD and impaired lung function at screening, and (3) the group with no previous COPD diagnosis, impaired lung function at screening, and who declined further assessment (Fig. 1).Opportunistic screening for COPD by social nurses has an impact on the use of COPD medication. This is assessed by examining number of prescriptions filled for COPD medications for two patient groups: (1) the group with no previous COPD diagnosis, impaired lung function at screening, and who underwent further assessment, and (2) the group of patients with previous diagnosed COPD at (Fig. 1). The reporting of medication will be organized into distinct categories, encompassing bronchodilators, corticosteroids, rescue medications, and maintenance therapies. Within each of these groups, the dosage prescribed or dispensed will be quantified.

Previous or no previous COPD diagnosis is assessed by the questionnaire at the time of screening as a patient-reported outcome. The lung function impairment is defined as FEV1/FVC ratio < 0.7. In the reporting, patients are stratified into groups with confirmed and non-confirmed COPD diagnosis.

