### Data collection

#### Baseline

Baseline data are derived from lung function measurements and the interviews and questionnaires completed at inclusion.

The data is sampled online by social nurses using a smartphone or tablet, and the data is directly entered into REDCap (Research Electronic Data Capture) [19]. Further, the results of the spirometry are uploaded directly from the smartphone to REDCap.

If online data entry is not possible, a paper version of the survey will be available. At the end of the inclusion period, they will be sent to the Department of Clinical Research at Hvidovre Hospital and entered manually into REDCap.

Upon reaching the necessary number of participants, the local investigators will refer to the outpatient bookings and physician notes in the electronic patient record, to determine whether the participants underwent further evaluation at a department of respiratory medicine and if a diagnosis of COPD was confirmed (as indicated by ICD10 coding J44).

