### Statistical considerations

Continuous variables will be presented as mean with standard deviation if the variable can be assumed to be normally distributed, otherwise, the median and interquartile range will be presented. Categorical variables will be presented with frequencies for each level and their corresponding percentages.

The prevalence of COPD in the study population will be compared to the prevalence in the Danish general population using an unadjusted test of the ratio of proportions, with a normal approximation of the logarithm of the ratio.

Since participants can die or otherwise drop out during the follow-up period, participants contribute with different follow-up lengths. The number of contacts in the follow-up period will therefore be reported as a rate (contact rate) of the number of contacts divided by the follow-up length, that is as contacts per year.

The healthcare contact rate will be compared among the three previously described COPD groups: undiagnosed COPD at inclusion who underwent further assessment, undiagnosed COPD without further assessment, and previously diagnosed COPD at inclusion, using a Poisson regression model. The model will include potential confounders as independent variables in addition to the COPD groups.

Sub-analyses for the rate of acute contacts and outpatient contacts will be conducted using models constructed in the same way as for all contacts.

Medication usage as a rate: number of prescriptions per year. Likewise, a Poisson regression model will be used to compare the rates among the COPD groups. However, the groups will be divided into no COPD versus diagnosed COPD. We will employ rigorous control for potential confounders. Specifically, age, smoking history, and comorbidities will be included as covariates in our models.

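### Group 3 of the five-year contact-rate comparison is defined by refusal in one place and by absence of assessment in another, so undiagnosed screen-positive patients who did not refuse but were never assessed have no fixed group

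*Protocol article*

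**What the plan says.** Four parts of the protocol article bear on who is in group 3.

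- **Five-year follow-up outcome measures.** Group 1 is "the group with no previous COPD diagnosis, impaired lung function at screening, and who underwent further assessment". Group 3 is "the group with no previous COPD diagnosis, impaired lung function at screening, and who declined further assessment". The same section sets lung function impairment at FEV1/FVC below 0.7.
- **Fig. 1 caption.** The third group is given as "3) COPD at inclusion who declined further assessment".
- **Statistical considerations.** "The healthcare contact rate will be compared among the three previously described COPD groups", which are then listed as "undiagnosed COPD at inclusion who underwent further assessment, undiagnosed COPD without further assessment, and previously diagnosed COPD at inclusion, using a Poisson regression model".
- **Data collection, Baseline.** To establish who was evaluated at a department of respiratory medicine, "the local investigators will refer to the outpatient bookings and physician notes in the electronic patient record".

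The Methods section also describes a way of not reaching the clinic that involves no refusal: "In cases where it is not feasible for patients to be seen at the respiratory outpatient clinic, they are instructed to contact their general practitioner". Under Outcome measures, the proportion examined at a respiratory clinic or by a GP within 4 months of screening is itself an outcome, so incomplete assessment is foreseen.

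**The concern.** Declining is an act by the patient. Being without assessment is a status with several possible causes, refusal being one. The statistical section says it takes over the groups already described, but its label for the third group covers more patients than the earlier definition.

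The difference matters for the second objective, the five-year impact of screening and referral. Group 2 had a COPD diagnosis before screening, so group 1 against group 3 is the only contrast among patients who were undiagnosed at screening. The two wordings give that contrast different comparators. If the wording stays open until the register data arrive, the choice could be made with outcomes in view.

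**Working it through.** **1. The plan's own figure.** The only design figure is the sample of 511 (Study design). With prevalences of 4.3% and 8.6%, two-sided 5% and 80% power, the pooled two-proportion formula is

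n = [1.96·√(2·p̄·(1−p̄)) + 0.8416·√(p0(1−p0) + p1(1−p1))]² / (p1−p0)², with p̄ = 0.0645.

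The numerator is (1.96 × 0.3474 + 0.8416 × 0.3461)² = 0.945 and the denominator is 0.043² = 0.001849. This gives about 511 (512 per group when rounded up), so the figure reproduces. It concerns the prevalence comparison and does not depend on how group 3 is defined. For scale, at the assumed prevalence 0.086 × 511 ≈ 44 participants with COPD would be spread over all three groups.

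**2. Where each undiagnosed patient with FEV1/FVC below 0.7 falls.**

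| Patient | Outcome section and Fig. 1 | Statistical considerations |
|---|---|---|
| Assessed | Group 1 | Group 1 |
| Refused assessment | Group 3 | Group 3 |
| Did not refuse, never assessed | No group | Group 3 |

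The third row includes, for example, a patient for whom a clinic visit was not feasible and who was not assessed by a GP, or one who did not attend after referral.

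**3. Which wording the data source supports.** The record review asks whether evaluation took place, so it separates seen from not seen. The article describes no recording of refusal. The described source therefore supports the statistical section's wording.

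**4. GP-assessed patients.** Outcome measures counts a GP examination as being examined. The record review looks only for evaluation at a department of respiratory medicine. A patient assessed by a GP would thus count as examined for the baseline outcome, but would appear unassessed if groups were built from the hospital record alone.

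**5. Illustrative size.** The article gives no refusal rate, attendance rate or relative contact rate, so all inputs here are assumptions. Let d be the share refusing (20–30%), a the share accepting but not seen (20–40%), the remainder seen (30–60%), and r the contact rate of those not seen relative to refusers.

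- Size of group 3, statistical section against outcome section: (d + a)/d.
- Crude rate of group 3 relative to refusers alone: (d + a·r)/(d + a).

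| Seen / d / a | Size ratio | r = 0.7 | r = 1.5 | r = 2.0 |
|---|---|---|---|---|
| 50 / 30 / 20 | 1.67 | 0.88 | 1.20 | 1.40 |
| 60 / 20 / 20 | 2.00 | 0.85 | 1.25 | 1.50 |
| 50 / 25 / 25 | 2.00 | 0.85 | 1.25 | 1.50 |
| 30 / 30 / 40 | 2.33 | 0.83 | 1.29 | 1.57 |
| 40 / 20 / 40 | 3.00 | 0.80 | 1.33 | 1.67 |

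Both quantities depend only on a/d, which runs from 20/30 to 40/20, so the first and last rows are the extremes. The crude rate ratio of group 1 to group 3 moves by the inverse of these factors: from 1/0.80 = 1.25 down to 1/1.67 = 0.60.

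**The case against.** The strongest reply is that declined is shorthand for not assessed. The statistical section says its groups are those already described, and the record review asks only whether evaluation occurred. On that reading nobody is dropped. The flowchart itself, the full protocol and any SAP are not shown, and any of them might assign these patients. The reply has weight: a reader might infer that patients who were never seen will be lost from the five-year analysis, and the article does not establish that. But nothing in it says that declined is shorthand, and the word stands in both the outcome definition and the figure caption. Two current passages of one document differ, and a later plan would have to depart from one of them.

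A second reply is that the size rests on invented inputs and is crude, whereas the model will include confounders. That stands, and the figures show only scale.

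A reader might also infer that non-attendance is the usual way referral fails in this population, or that refusers will be few. The article supports neither. Nor does the statistical section's label take in every unassessed participant; it covers only those with undiagnosed COPD.

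A third reply is that a definition based on hospital bookings within 4 months would create problems of its own. It would place GP-assessed patients among the unassessed. Since follow-up runs from inclusion, it would also credit group 1 with time during which its members had to survive to be seen. Both points are right, and the change proposed here allows for them.

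**Conclusion.** The inconsistency is real and should be resolved before the follow-up data are analysed. It decides whether undiagnosed screen-positive patients who did not refuse but were never assessed enter the only contrast among the undiagnosed. The described data source favours the statistical section's wording.

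The size cannot be established from the article. Under the stated assumptions, group 3 is about 1.67 to 3.0 times larger under the wider definition. Its crude rate, before covariate adjustment, changes by a factor of 0.80–0.88, 1.20–1.33 or 1.40–1.67 when those not seen have 0.7, 1.5 or 2.0 times the refusers' rate. If the two kinds of patient had the same contact rate, only the size of the group would change. The prevalence objective and the sample size stand as they are.

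**What to change.** - Use one status-based definition of group 3 in the Fig. 1 caption, Five-year follow-up outcome measures and Statistical considerations: no previous COPD diagnosis, FEV1/FVC below 0.7 at screening, and no further assessment for any reason.
- State where GP-assessed patients belong and from what source their assessment will be known, so that Outcome measures and the record review agree.
- If a time window is used to classify patients, such as the 4 months already used for the baseline outcome, start follow-up for group 1 against group 3 at the end of that window (a landmark), or treat assessment as time-varying. Otherwise group 1 gains immortal time.
- Where the records show why a patient was not assessed, report the comparison with refusers alone as a sensitivity analysis.

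The cost is a change of wording in three places, a rule for GP-assessed patients, and a note of the reason, where available, in a record review that is already planned. The downsides are a more mixed group 3 and, with a landmark, a slightly later start of follow-up.

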**Methods:**

The present prospective longitudinal study includes a clinical examination at baseline. Participants will have spirometry done and be interviewed regarding risk factors, socioeconomic conditions, and respiratory symptoms. The 5-year follow-up assessment incorporates data from baseline and register data over the 5 years, including information on morbidity, use of COPD medication, hospital contacts, mortality, and socioeconomic factors.

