### Outcome measures

From the baseline examination, the study will report the following outcome measures:Prevalence of non-reversible airflow limitation that is a post-bronchodilator FEV1/FVC ration< 0.70Proportion of diagnosed vs. undiagnosed COPD at the time of screening (with a previous diagnosis of COPD defined as a patient-reported diagnosis in the baseline questionnaire)Proportion of patients diagnosed with lung function impairment (FEV1/FVC ratio < 0.7) subsequently examined at a respiratory outpatient clinic/GP within 4 months from screening.Prevalence of patients diagnosed with COPD after screening (identified by ICD10 code J44, or redeemed prescriptions of COPD treatment)Prevalence of participating current smokers who wish to stop smoking (patient-reported outcome in the baseline questionnaire)Prevalence of patients with identified lung function impairment (FEV1/FVC ratio < 0.7) at screening, who have a desire to quit smoking (patient-reported outcome in the baseline questionnaire)Prevalence of patients who want to quit smoking (patient-reported outcome in the baseline questionnaire) and accept the smoking cessation support offers (identified by social nurse notes in patient report).

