#### Clinical variables

The patients enrolled in this study may be categorized into four groups according to their diagnostic status: those previously diagnosed with COPD (self-reported), those identified as having COPD through screening, those without COPD as determined by screening, and those with an unknown diagnostic status due to insufficient lung function test. COPD identified through screening refers to people whose post-bronchodilator FEV1/FVC ratio is less than 0,7, according to the measurements obtained by the social nurse.

When assessing the prevalence of COPD, the groups diagnosed through screening and self-reported COPD are considered. Participants who are unable to perform spirometry are classified as having an unknown diagnostic status and are not included in the calculation of COPD prevalence.

At the 5-year follow-up, the prevalence of patients diagnosed with COPD after screening is identified either through the National Patient Health registry based on the ICD10 code J.44 or by examining prescriptions for COPD medication (including all types of inhalation medicine) recorded in The Danish National Prescription Database.

The utilization of healthcare services is evaluated based on all hospital contacts, including outpatient visits, admissions, and emergency department (ED) visits.

Admission diagnosis and department will be included as descriptive variables - partly to ascertain whether there are patterns in where the screening has the greatest impact, and partly to assess whether there is selection bias in the study.

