## Discussion

Our study is a pragmatic clinical study involving a marginalized patient population that is often excluded from participating in clinical trials due to lower health literacy and marginalization [23].

A potential methodological limitation in this study is the possibility of measurement errors arising from the use of social nurses rather than nurses with specialized respiratory training to conduct spirometry. To mitigate these risks, training is provided through local respiratory medical staff. Additionally, the social nurses are also required to be familiar with the Danish standard for lung function testing [24]. Moreover, social nurses interact directly with five to eight patients during a day shift, based on a subjective assessment of which patients need the most attention. This results in a carefully selected group of marginalized patients, potentially introducing selection bias between the study sites.

Furthermore, the handheld technical equipment used for performing the lung function test may increase the risk of measurement errors. Hence, we cannot make a definite diagnosis of COPD, but detect a possible impairment or obstructive pattern in the spirometric values. When suspicion of lung disease arises, patients undergo the standard diagnostic procedure at the current hospital, with some patients assessed in the outpatient clinic and others referred to their general practitioner. Since we cannot retrieve diagnosis from general practitioners, diagnosis verification is only available for those who attend the outpatient clinic. The five-year follow-up will determine if patients receive regular prescribed medication, facilitating confirmation of the COPD diagnosis.

We employ post-BD spirometry utilizing airflow limitation as the criterion for COPD diagnosis. Although COPD is the predominant cause of irreversible airflow limitation, it is noteworthy that a minority of patients, including those with conditions such as bronchiectasis, cannot be entirely ruled out from our study cohort. Further, an essential consideration involves the exclusion of individuals with severe, acute illnesses from the assessment of COPD prevalence due to their inability to actively participate in lung function measurements.

A strength of the study is the use of a multi-centre design on a national level, which thus with a high degree of validity reflects this subgroup of the Danish population.

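### Previous COPD rests on self-report alone, while diagnosis after screening is any J44 code or inhaler prescription, so existing cases can be counted as found after screening

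*Protocol article*

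**What the plan says.** **Before screening.** The Outcome measures section separates diagnosed from undiagnosed COPD "with a previous diagnosis of COPD defined as a patient-reported diagnosis in the baseline questionnaire". The Five-year follow-up outcome measures section uses the same source to form the follow-up groups: "Previous or no previous COPD diagnosis is assessed by the questionnaire at the time of screening as a patient-reported outcome". Clinical variables also describes earlier COPD as self-reported.

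**After screening.** Outcome measures lists, among the results of the baseline examination: "Prevalence of patients diagnosed with COPD after screening (identified by ICD10 code J44, or redeemed prescriptions of COPD treatment". Clinical variables puts the determination later, "At the 5-year follow-up, the prevalence of patients diagnosed with COPD after screening is identified either through the National Patient Health registry", and makes the prescription route broad: "prescriptions for COPD medication (including all types of inhalation medicine) recorded in The Danish National Prescription Database".

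**Register period.** The Abstract says: "The 5-year follow-up assessment incorporates data from baseline and register data over the 5 years". The Five-year follow-up part of Data collection plans linkage by civil registration number to the patient, cause-of-death and prescription registers. It mentions no period before inclusion.

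**Groups.** Group 1 reports no previous COPD, has impaired lung function (FEV1/FVC < 0.7) and was assessed further. Group 2 was previously diagnosed. Group 3 reports no previous COPD, has impaired lung function and declined assessment. Contact rates are compared across all three groups; the prescription outcome is defined for groups 1 and 2.

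**The concern.** The two sides of the before/after contrast use different instruments: recall before screening, registers after it. Nothing in the stated rules removes a person whose register history began before inclusion. A refill of a long-standing inhaler, or a repeat J44 code at a later contact, meets the definition of a diagnosis after screening although nothing new was found. Read literally, the outcome even admits people who did report COPD at baseline.

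Three results are exposed:

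- **The undiagnosed proportion**, because unreported earlier cases are added to it.
- **The apparent yield of screening**, because the same people reappear as diagnosed afterwards.
- **The group comparisons behind the second objective**, because established COPD, with its contacts and prescriptions, enters groups meant to contain newly found disease. Covariate adjustment does not repair a misclassified group label.

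Under-reporting is plausible. Participants are interviewed in hospital, and the Discussion gives lower health literacy as one reason why such patients are often left out of trials.

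**Working it through.** **1. Definitions side by side**

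| Element | Before screening | After screening |
|---|---|---|
| Source | Questionnaire | Patient register or prescription register |
| Evidence | Patient says COPD | J44, or any redeemed inhaled medicine |
| First event required? | Not applicable | Not stated |
| Limited to people without earlier COPD? | Not applicable | Not stated |
| Period | Recall at inclusion | Listed under baseline in one section, at 5 years in another |

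Take a person with an inhaler prescription running before inclusion, FEV1/FVC < 0.7, and no COPD reported. The questionnaire rule gives no previous diagnosis. The spirometry rule gives group 1 or 3. The next refill gives diagnosed after screening. Each step follows from a stated rule.

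**2. The plan's own figure**

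Inputs (Study design): background prevalence 4.3%, twofold ratio so 8.6%, power 80%, significance level 0.05. The pooled two-sample, two-sided formula with mean proportion 0.0645 is

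n = [1.960·√(2·0.0645·0.9355) + 0.842·√(0.086·0.914 + 0.043·0.957)]² / 0.043²
= (0.6809 + 0.2912)² / 0.001849 ≈ 511 per group.

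This reproduces the stated 511. The point does not depend on that calculation; it uses 511 only as the number of participants.

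**3. Number of people with COPD who could be misplaced**

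- Expected cases: 0.086 × 511 = 43.9, about 44. This takes all 511 as having usable spirometry.
- Assumptions, not in the documents: 20% to 50% of cases were diagnosed before, and 5% to 30% of those do not report it.
- Low end: 44 × 0.20 × 0.05 = 0.4.
- High end: 44 × 0.50 × 0.30 = 6.6, about 7.

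Effect on the undiagnosed proportion, with no error in the other direction:

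- Low end: (35.2 + 0.44)/44 = 81% instead of 80%.
- High end: (22 + 6.6)/44 = 65% instead of 50%.

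**4. Share of apparent new diagnoses that already existed**

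Per 100 people with airflow limitation, add two assumptions: 20% to 60% of the truly undiagnosed receive a diagnosis, and every unreported earlier case has a later code or prescription. Count only people who report no COPD.

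- Low: 20 earlier cases, 5% unreported, 60% newly diagnosed. 1/(1 + 48) = 2%.
- Middle: 50 earlier, 20% unreported, 40% newly diagnosed. 10/(10 + 20) = 33%. The apparent diagnosis rate is 30/60 = 50% instead of 40%.
- High: 50 earlier, 30% unreported, 20% newly diagnosed. 15/(15 + 10) = 60%.

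**5. Inhaler users without COPD**

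People who take inhaled medicine for another reason, such as asthma, and have FEV1/FVC of 0.7 or more cannot enter groups 1 to 3. They can still meet the prescription rule for diagnosis after screening. The documents give no basis for their number.

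**The case against.** **The rules are open, and self-report has merit.** It can capture diagnoses made only in general practice, which the registers miss. The Discussion admits the limit: "Since we cannot retrieve diagnosis from general practitioners, diagnosis verification is only available for those who attend the outpatient clinic". Reporting is to be stratified by confirmed and non-confirmed diagnosis, and the Discussion speaks of regular medication: "The five-year follow-up will determine if patients receive regular prescribed medication, facilitating confirmation of the COPD diagnosis". These points stand, but none of them checks for a diagnosis or prescription before inclusion. The word regular also does not appear in the outcome definitions themselves.

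**First-event rules and look-back length may sit in a fuller document.** That is fair for the length of a look-back. But the self-report rule and the any-code-or-prescription rule are stated outright and define named outcomes and groups. An analysis that followed them would carry the problem forward.

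**The timing can be read without contradiction.** The Baseline part of Data collection has investigators check bookings and notes for J44 once enrolment is complete, and the register ascertainment comes at 5 years. A reader might infer that Outcome measures and Clinical variables flatly contradict each other. Two time points for one outcome is also a fair reading. What remains is that the early check does not mention prescriptions and has no fixed window. With recruitment from April 2021 to an anticipated 2024, it gives early participants about three years and late ones almost none.

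**The direction is not certain.** A patient with airflow limitation who wrongly reports earlier COPD lowers the undiagnosed proportion. This stands.

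**The size is easily exaggerated.** A reader might apply an unreported rate of 5% to 10% to all 511 participants, get 26 to 51 people, and conclude that the error is as large as the whole expected COPD group of 44. The documents do not support that. At the upper end unreported earlier cases would outnumber all COPD cases, which is possible only if many are inhaler users without COPD, and those without airflow limitation cannot enter groups 1 or 3.

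**Conclusion.** The concern holds as a defect in stated definitions that can produce a wrong result. Existing cases can be credited to screening. A reader might infer that they certainly are, but no under-reporting rate is documented.

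On the assumptions shown, about 0.4 to 7 of 44 people with COPD would be misplaced, plus an unknown number of inhaler users without COPD counted as diagnosed. The counts are small, but they can be a large share of the apparent new diagnoses: 2% to 60% across the assumed ranges. The sample size and the prevalence comparison it supports are unaffected. The definitions should be changed before the register extraction, while this is still cheap.

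**What to change.** - Extend the planned register extraction to a stated period before each patient's inclusion date.
- Count a diagnosis after screening only as a first J44 code or first COPD prescription after inclusion, in people with no self-reported COPD and no earlier J44 code or COPD prescription.
- Class patients with a J44 code before inclusion as previously diagnosed, alongside self-report.
- Repeat the group comparisons and the undiagnosed proportion in two sensitivity analyses: one that also counts earlier prescriptions as previous COPD, and one with self-report alone. Earlier prescriptions should not be in the main definition of previous COPD, because earlier inhalers may be for asthma and would then remove truly new COPD from groups 1 and 3.
- State one fixed window from each patient's inclusion date for the early figure, and report the 5-year cumulative figure separately. The 4 months in Outcome measures apply to being examined and should not simply be taken over for diagnosis.
- Reconcile Outcome measures, the Baseline part of Data collection and Clinical variables on timing and source, and settle whether any prescription or regular use is meant.

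The cost is slightly more register work within linkage already planned, and a reported screening yield that is likely to be less favourable. No new patient contact is needed, and the 511 does not change.
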